#### Follow-Up Assessment

All participants are followed up at 1 month, 6 months, and 1 year after enrollment on the internet or telephone (Table 3). We have established a follow-up system to direct and supervise the participants for better communication, feedback, and compliance. Unscheduled visits for any reason, as well as delayed visits within 7 days of the visit window, are recorded. If a participant reports ischemic symptoms, such as the sudden onset of disorder of motility or sensation, headache, dizziness, imbalance, epilepsy, and/or disorders of consciousness, we will arrange examinations of MRI or CT immediately for the patient and evaluate whether the therapy strategy should be altered. All cerebral arteries including extracranial and intracranial arteries are evaluated per patient at follow-up. During the follow-up period, the drug compliance evaluation scale are also be assessed.

**Table 3 T3:** The planning of the follow-ups.

	**Screening period**	**Follow up period**			
**Visit time**	**Before intervention**	**1 m ±7 d**	**6 m ±7 d**	**12 m ±7 d**	**Unscheduled visit**
Informed consent	√				
Inclusion and exclusion criteria	√				
MRI DWI	√	√*	√*	√*	√
CTA/MRA/DSA	√				
MRI ASL	√				
mRS	√	√	√	√	√
Medical and medication history	√				
Medication	√	√	√	√	√
Intracranial ischemic event		√	√	√	√

*√*The examination will be done when intracranial ischemic event occurs*.

### Data Collection and Management

Data for patients enrolled in the study are collected through electronic case report forms. All de-identified data, including demographics, cerebrovascular events, lesion characteristics, and laboratory examination results, are collected by physicians at study entry and patient follow-up. All participants are expected to complete study visits over the planned 1-year follow-up period. In addition, this study is supervised by an independent Data Safety Monitoring Board (DSMB) that comprises independent experts from neurology, neuroradiology, and neurosurgery. The DSMB oversees the study by training and certificating the study staff, reviewing the general conduct of the trial, and checking the study data for quality and safety. Comprehensive training and regular assessment are carried out for all study staff to standardize data collection and assessment. The DSMB also gives suggestions for continuation, modification, or termination of the study. All adverse events that occurred during the study period are reported to the DSMB.

### Sample Size

By referring to the published study on medical management in patients with ICAD under 50 to 99% stenosis, the 1-year recurrence incidence of ischemic stroke is assumed to be 8.98% (5). The hazard ratio of hemodynamics (normal or compromised), which is a major risk factor for stroke, is assumed to be 2.4 (26). In addition, the loss rate of follow-up is assumed to be 10%. Thus, the study needs to recruit around 400 participants.

### Statistical Analysis

The results will be analyzed with the intention-to-treat method. All confounding factors that influenced outcomes will be analyzed, such as demographic data, cerebrovascular events, lesion characteristics, and laboratory examination results. Student *t*-test will be used for continuous variables, while the Mann-Whitney test will be used for ordinal variables. Count data of categorical variables will be analyzed by the Chi-square test or Fisher's exact probability method. *P* < 0.05 is considered statistically significant.

Subsequent multivariate analysis by logistic regression will be performed to detect independent relevant factors influencing primary endpoints. The regression coefficient of independent variables is defined as the weight of this variable for an evaluation system. If there are difficulties for building an evaluating system by the logistic regression model, we will attempt to establish the decision tree with high sensitivity for the evaluation system by Random Forest regression (34).

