## Methods and Analysis

### Study Design

This is a prospective, longitudinal, and nested case-control study of patients with ICAD who are treated with aggressive medical therapy in a tertiary hospital in northern China (Trial Registration No: ChiCTR2100048832) (Figure 1). This study aims to (i) identify multimodal imaging predictors of refractory to medical treatment of high-risk patients with ICAD and (ii) explore and validate a refined risk stratification model for patients with ICAD based on the above multimodal imaging predictors.

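### Fitted logistic coefficients become the score weights with about 32 expected events and about 11 imaging candidates, so the weights are likely to be too extreme; the promised validation has no described step

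*Protocol article*

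**What the plan says.** Under Statistical Analysis, t, Mann-Whitney and chi-square or Fisher tests come first, with 0.05 as the significance level. A multivariable logistic regression follows, and then the weighting rule: "The regression coefficient of independent variables is defined as the weight of this variable for an evaluation system". The clinical candidates are open-ended: "All confounding factors that influenced outcomes will be analyzed, such as demographic data, cerebrovascular events, lesion characteristics, and laboratory examination results". If the logistic model proves difficult, "we will attempt to establish the decision tree with high sensitivity for the evaluation system by Random Forest regression".

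Baseline Evaluations and Data Collection names the imaging measures:
- **Lumen:** degree of stenosis, lesion location, lesion length.
- **Plaque:** remodeling index, plaque burden, signal intensity.
- **Perfusion on ASL:** hypoperfusion, arterial transit artifact.
- **Flow simulation:** translesional pressure drop, wall shear stress, LDL filtration rate.

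Sample Size considers one binary factor: "The hazard ratio of hemodynamics (normal or compromised), which is a major risk factor for stroke, is assumed to be 2.4". It adds that "the 1-year recurrence incidence of ischemic stroke is assumed to be 8.98" per cent, allows 10% loss to follow-up, and concludes: "Thus, the study needs to recruit around 400 participants".

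Study Design gives the second aim as to "explore and validate a refined risk stratification model for patients with ICAD based on the above multimodal imaging predictors". The Abstract's statement of that aim has only the exploring part.

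**The concern.** The score is the main product of the study. When a logistic model is fitted by maximum likelihood to few events per candidate, its coefficients tend to lie too far from zero. Using them directly as weights spreads predicted risks too widely, can keep noise variables as independent factors, and makes the model look better in its own data than it will in new patients. The Discussion wants the score to pick out patients at high risk under medical treatment, so predictions that are too extreme would misstate the very quantity the study sets out to give. A random forest is more flexible than a logistic model and needs no fewer events. A stated aim of validation also leads readers to expect evidence that the article gives no means of producing.

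**Working it through.** **The plan's own figure.** Events for one binary factor = (z_α + z_β)² / [p(1−p)(ln HR)²]. With HR 2.4 and half the patients exposed, the denominator is 0.25 × 0.8755² = 0.1916.
- Two-sided 5%, 80% power: 7.849 / 0.1916 = 41 events; 41 / 0.0898 = 457; 457 / 0.90 = 508 patients.
- One-sided 5%, 80% power: 6.183 / 0.1916 = 33 events; 33 / 0.0898 = 368; 368 / 0.90 = 409 patients.

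Sidedness, power and exposure prevalence are not stated, so 400 can be matched only by assuming them. What matters here is that the sizing concerns one factor and not a multivariable score.

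**Events available.** 400 × 0.90 × 0.0898 = 32.3 (35.9 with no loss). The true count may differ: 8.98% is for recurrent ischemic stroke, while the endpoint is limited to the target-vessel lesion and adds attributable death. As an upper range, the Introduction's 12.2% to 23% per year for severe stenosis would give 360 × 0.122 = 43.9 to 360 × 0.23 = 82.8 events.

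**Events per candidate.** The list under Baseline Evaluations comes to about 11 measures: 32.3 / 11 = 2.9. The upper range gives 43.9 / 11 = 4.0 to 82.8 / 11 = 7.5. Each clinical or laboratory variable lowers the ratio further; 20 candidates, an illustrative total, give 32.3 / 20 = 1.6.

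**Expected shrinkage.** The maximum Cox-Snell R² at 8.98% events is 0.453. I assume a true R² of 15% to 30% of that and solve N = k / [(S − 1) ln(1 − R²/S)], where k is the number of parameters and S the expected shrinkage factor.

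| Parameters | Events per parameter | S at N = 360 | Evaluable N for S ≥ 0.90 |
|---|---|---|---|
| 3 | 10.8 | 0.90–0.95 | 184–382 |
| 10 | 3.2 | 0.72–0.84 | 611–1,273 |
| 12 | 2.7 | 0.68–0.82 | 733–1,528 |
| 20 | 1.6 | 0.57–0.73 | 1,221–2,546 |

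**Simulation.** 360 patients, about 9% events, a few true predictors and the rest noise, unpenalised logistic regression, tested in new data. Effect sizes and correlations are assumptions and differ between rows.

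| Candidates | Screen at 0.05 | Apparent AUC | AUC in new data | Calibration slope |
|---|---|---|---|---|
| 10 | yes | 0.68 | 0.61 | 0.64 |
| 10 | no | – | – | 0.49 |
| 11 | with or without | 0.70–0.74 | 0.63 | about 0.5–0.6 |
| 12 | yes | 0.70 | 0.63 | 0.62 |
| 20 | yes | 0.70 and 0.71 | 0.60 and 0.62 | 0.47 and 0.52 |
| 20 | no | 0.78 | 0.60 | 0.30 (0.26 in a second setting) |

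The AUC gap runs from 0.70 − 0.63 = 0.07 to 0.78 − 0.60 = 0.18. A slope of 0.5 means that the log-odds are spread 1 / 0.5 = 2 times too widely.

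**Aim against method.** Study Design promises validation and the Abstract does not. The study is single-centre, and the article describes no split sample, resampling or second cohort.

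**The case against.** The strongest reply is that a journal article condenses a fuller protocol, and an analysis plan could add a cap on candidates, shrinkage and resampling. That is fair for the omissions: the absence of a calibration measure or a bootstrap here is not in itself a fault. It does not remove the weighting rule, which the article states outright, or the difference between its two statements of the aim.

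Several stronger readings are tempting, and the document does not support them.
- **P < 0.05 as an entry filter.** The order of the steps suggests it, but 0.05 is given only as the general significance level. The conclusion does not depend on it, since fitting all candidates unscreened did worse. That the coefficients are unpenalised is likewise inferred, because no penalty is mentioned.
- **The outcome used as a predictor.** A reader might infer this because cerebrovascular events appear among the factors and data "are collected by physicians at study entry and patient follow-up". But the imaging is required at recruitment, and Table 3 places the baseline imaging and medical history at screening. Prior stroke or TIA is the natural reading, so only a clarification is warranted.
- **Certain overfitting, or a model that will never be validated.** The degree of overfitting depends on how many candidates are finally considered. The article fixes no total; 20 is illustrative, and nothing says that all 11 imaging measures must enter one model. Nor does anything rule out resampling or a later cohort.

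The random forest is a conditional fallback, so it is secondary. A three-parameter core also sits uneasily with the first aim of finding predictors among many measures, which is why the remaining candidates should stay in as exploratory.

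**Conclusion.** The point stands in a limited form. With about 32 events and about 11 imaging candidates plus open clinical groups, taking fitted coefficients as weights is likely to give a score that is too extreme. The calibration slope is roughly 0.5 to 0.65 for 10 to 12 candidates. For 20 it is roughly 0.3 to 0.6: simulated values run from 0.26 to 0.52, and the analytic range starts at 0.57. Apparent AUC would be inflated by about 0.07 to 0.18. These sizes rest on assumed effects, an assumed R² range, and most candidates being considered. At the plan's assumed event rate, about three pre-specified parameters can be supported. Separately, the claim to validate has no described step behind it and differs from the Abstract.

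**What to change.** In Statistical Analysis:
- Pre-specify a small core model matched to about 32 events: about three parameters, for example one each for stenosis, plaque and hemodynamics. Label the other candidates exploratory.
- Define the weights as penalised or shrunken coefficients, and use that penalised model in place of the random-forest fallback.
- Report bootstrap optimism-corrected discrimination and calibration slope, repeating every modelling step in each resample.
- State, as a clarification only, that predictors are values at enrolment.

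In Study Design, change *validate* to *internally validate*.

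No extra patients or data are needed. The cost is some programming and rewording, a less favourable reported AUC, and fewer predictors claimed as independent. The changes should be settled before outcome data are analysed.

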## Discussion

Intracranial atherosclerotic disease is the primary cause of stroke, especially in Asia, which caused high burdens of mortality and morbidity despite the latest treatment strategies, including medical management, endovascular treatment, and surgery (5). The effect of medical management seems ideal for a majority of patients with ICAD, while the current evaluation system cannot accurately predict those with a high risk of recurrent stroke under aggressive medical management (35). Although recurrent stroke is the multifocal cause in patients with symptomatic ICAD, studies have shown that the culprit lesion of ICAD was the major cause (36). Therefore, treatment for ICAD should be mainly focused on the culprit lesion. For the patients' refractory to medical management, other therapy strategies, such as endovascular treatment or surgery with direct intervention, has been adopted according to the current guideline recommendation (8, 13).

However, early diagnosis of high-risk patients' refractory to medical treatment and early triage to alternative therapy is limited by the current risk stratification system, which is merely based on the degree of luminal stenosis (37). The inclusion of the plaque characteristics and hemodynamics assessment with multimodal imaging method may provide a potential solution to make accurate risk stratification (22). To the best of our knowledge, the current study will be the first research to involve multimodal imaging evaluation from three aspects, including the degree of luminal stenosis, plaque characteristics, and hemodynamics, and plan to establish the prognosis prediction system for patients with ICAD who have medical treatment.

As an observational study, several potential limitations must be considered. The collected data may not be as robust as randomized control studies with blinding performance, while the randomized control studies may be needed to further confirm the results of the present study. Data collection and analysis will perform repeated verification and blinding assessment, respectively. Moreover, the study population will be focused on Chinese patients with ICAD; hence, caution must be applied when implementing the findings of this study in other ethnicities.

### Ethics and Dissemination

This study has been approved by the ethics committee of our center ([2021]083) and was prospectively registered (Registration No: ChiCTR2100048832). This study will be conducted according to the principles of the Declaration of Helsinki and subsequent amendments (29, 30). Study findings will be disseminated through peer-reviewed publications and presentations at scientific meetings.

## Ethics Statement

The studies involving human participants were reviewed and approved by the Ethics Committee of Xuanwu Hospital. The patients/participants provided their written informed consent to participate in this study.

